#### Screening 

The medical management of the cooperating clinics will provide the screening of inclusion criteria. If the inclusion criteria are met, the child and significant other will receive the recruitment information. The information material and consent forms are specially designed for children; if they are not yet able to write themselves, their parents or guardians do this on their behalf. The child’s consent is a prerequisite for the realization of each session. They can refuse to participate at any time. After having obtained informed consent, the child-significant other dyad will be randomly assigned to one of the three study arms and informed about their assignment. Together with the interprofessional team of the responsible clinic, it will be decided whether the music therapy will take place on an outpatient basis, i.e. the Nordoff/Robbins Music Therapy Centre, Witten, or on an inpatient basis in the clinics, either in the music therapy unit or on the hospital wards.

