#### Baseline (pre-T1, T1/T2)

The paper–pencil baseline survey will be completed by all children (approx. 10 to 15 min) and significant others (approx. 20 to 30 min) (pre-T1), i.e. up to a maximum of 3 days prior to the APCI with its two manualized entry music therapy sessions (approx. 25 min each) (T1/T2). The APCI music therapy sessions will be video-recorded and evaluated using the APCI online programme. APCI raters are blinded and will give information about possible significant moments in T1/T2 and about their adherence to the APCI manual based on self-evaluation. The child and significant other will also provide information about their significant moments if present. Two independent student raters will rate one of the two APCI sessions for APCI manual adherence.

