### Randomization

#### Treatment allocation

We will use block randomization of 10 to 12 child-significant other dyads each. From the total of 52 child-significant other dyads to be included, 21 dyads will be randomly assigned to the INMUT-KB, 21 dyads to MUT-K, and 10 dyads to WLG. The randomization plan will be carried out by an independent research assistant at the Heidelberg University Hospital, who is not otherwise involved in the study, using the statistical software R version 4.2.1 [36, 37]. The randomized allocation of the child-significant other dyads into the three study arms will be performed after finalization of the screening. The allocation will be carried out by means of sealed envelopes (“sealed envelope method”), which will be opened in the presence of the child-significant other dyads together with a study staff member.

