### Measures

As the purpose of this study is to explore the feasibility of a fully powered RCT, we will use different measures, including both qualitative information and quantitative data.Feasibility and acceptability of research methodology*RQ1.1*: The feasibility analysis of the protocol implementation focusses on the overall recruitment target of the child-significant other dyads (*n* = 52), as well as the specific recruitment target for each study-arm INMUT-KB (*n* = 21), MUT-K (*n* = 21), and WLG (*n* = 10). The study considers the estimation of the total sample to be recruited, the overall dropout rate, and the differentiated dropout rate within the study arms at all measurement times. Data will be collected by observing the participant flow: Counting the number of study participants who (1) are recommended for inclusion by the medical team; (2) are contacted by the study staff to provide information about the feasibility RCT; (3) give their consent to study participation; (4) will be included into the study; (5) drop out before the baseline survey (pre-T1); (6) complete the baseline survey (pre-T1); (7) drop out before or during the baseline APCI ratings (T1/T2); (8) complete the baseline APCI ratings (T1/T2); (9) drop out before or during the INMUT-KB, MUT-K, and WLG (T3–T9); (10) complete INMUT-KB, MUT-K, and WLG (T3–T9); (11) drop out before the final APCI rating (T10); (12) complete the final APCI rating (T10); (13) drop out before the outcome survey (post-T10); (14) complete the outcome survey (post-T10); (15) drop out before the 3-month follow-up survey (cat-T11); and (16) complete the 3-month follow-up survey (cat-T11). We will describe the causes for dropout and calculate the retention rate for the three study arms separately and together. Success is defined as attaining 100% and retaining 75% of the planned sample.*RQ1.2*: The feasibility of this RCT depends on the recruitment of a sufficient number of music therapists. We expect around five to six cases per music therapist, so that successful recruitment will involve at least seven to eight music therapists. For professional support, every third session will be supervised; based on the case numbers, we are planning 108 supervised sessions.*RQ1.3*: Certification to use the APCI was started by seven music therapists and successfully completed by five. The APCI raters were trained in the practical application of the APCI manual, video analysis, data collection, and statistical analysis. Experience-based receptive interviews [43] with APCI raters will gather information about the circumstances that contribute to successful APCI implementation. The success of APCI blinding will also be evaluated in receptive interviews. For professional support, every third APCI session will be supervised; based on the case numbers, we are planning 49 supervised sessions.

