#### Estimation of effect sizes

For *estimation of effect sizes*, and because child-significant other dyads treated by one music therapist (within-group) may be more like each other compared to those treated by another music therapists (within-group), a two-level linear regression analysis will be performed to account for potential clustering effects at higher levels (i.e. child-significant other dyads nested within therapists). The intraclass correlation (ICC) coefficient from the random intercept model with child-significant other dyad (Level 1) and therapist (Level 2) will be calculated for the proposed primary outcome (APCI) [59]. An ICC greater than zero will indicate a clustering effect, and any statistical analysis must be adjusted for these effects. All proposed outcomes will be analysed as intention to treat (ITT; *n* = 52) using mean scores (*M*), standard deviations (*SD*), and 95% *CI*. The ITT calculation will be regardless of whether the child-significant other dyads will violate the inclusion criteria, whether they complete the music therapy, or whether they will withdraw from the study due to protocol deviations (e.g. concurrent music therapy during the study period [60]). Missing values of less than 20% will be replaced with the conditional mean value of the subgroups (INMUT-KB, MUT-K, WLG). This will be compared to per-protocol analyses. We will use mixed-design ANOVAs (group: INMUT-KB, MUT-K, WLG; status: child-significant other dyad, child alone; time: baseline, post-intervention, 3-month follow-up), adjusting for baseline scores considering demography as well as outcome data. Because treatment outcome will be measured at three assessment points, within-group effects will be further analysed by comparisons between baseline and post-intervention (Contrast A) and by comparisons between post-intervention and 3-month follow-up (Contrast B) (RQ3.1). Effect sizes will be presented as partial eta-squared values (η^2^) and Cohen’s *d*, calculated as the difference between the means divided by the pooled standard deviation $$(d=\frac{{x}_{1}^{2}-{x}_{1}^{2}}{\sqrt{{s}_{1}^{2}+{s}_{2}^{2}}/2})$$. Classification of *effect sizes* will be as follows: η^2^ ≥ 0.010, small effect; η^2^ ≥ 0.060, medium effect; η^2^ ≥ 0.140, large effect; Cohen’s *d* 0.20, small effect; *d* ≥ 0.50, medium effect; and *d* ≥ 0.80, large effect [61] (RQ3.2, RQ3.3).

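### Dyads learn their arm before the pre-T1 self-reports and the baseline APCI, yet the analysis treats these values as ordinary baselines

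*Protocol article*

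**What the plan says.** All references are to the protocol article.

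- **Screening:** after informed consent, "the child-significant other dyad will be randomly assigned to one of the three study arms and informed about their assignment".
- **Treatment allocation:** allocation "will be performed after finalization of the screening", using sealed envelopes "which will be opened in the presence of the child-significant other dyads together with a study staff member".
- **Table 2:** the screening column holds only the clinical diagnosis and cancer treatment. Demographics, GAS, KINDL, EXIS, BAS, SCL-9k and WIRF are first collected at pre-T1, and the APCI at T1–T2.
- **Baseline (pre-T1, T1/T2):** the survey is timed against the first APCI session, "i.e. up to a maximum of 3 days prior to the APCI with its two manualized entry music therapy sessions". It is not timed against allocation.
- **Measures, RQ1.1:** the participant flow counts inclusion (item 4), then drop-out before the baseline survey (item 5), then completion of that survey (item 6).
- **Blinding:** dyads know their arm and the study's general aims, but not the hypotheses for any endpoint. APCI raters are blinded and are not the dyad's own therapists.
- **Estimation of effect sizes:** mixed-design ANOVAs are run "adjusting for baseline scores considering demography as well as outcome data". Contrast A compares baseline with post-intervention; Contrast B compares post-intervention with the 3-month follow-up.

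**The concern.** A baseline is useful as a starting point or covariate because allocation cannot have influenced it. Here the family sees the envelope opened, learns whether it has joint therapy, child-only therapy or a wait, and only then fills in the self-reports and attends the first APCI. Relief or disappointment could move the self-reported values differently by arm.

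GAS is the clearest case. Child and significant other write their goals in free text, and these are sorted into categories that include interpersonal goals. A family that knows the significant other will be in the room may write different goals from one that knows the child will attend alone. Goal content can then differ by arm before any therapy has been given.

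At stake are the effect-size estimates for RQ3.1 to RQ3.3. The article intends to use efficacy trends from this study to calculate the size of the confirmatory trial, and that trial might inherit the same order of steps.

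**Working it through.** **Order of events.** The documents give no figure to reproduce, so the check is one of sequence.

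1. Consent, then allocation and disclosure (Screening).
2. The trigger for allocation is the end of screening (Treatment allocation), and by Table 2 screening contains no outcome measure.
3. Pre-T1 falls at most 3 days before T1 (Baseline), and T1/T2 follow.
4. The flow list allows for drop-out between inclusion and pre-T1, which fits the same order.

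No sentence says outright that the baseline follows randomisation, and Fig. 1 is not shown. But all the available text agrees, and none of it places an outcome baseline before allocation.

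**What a shift would do.** These inputs are all assumptions; the documents give none of them:

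- s: the shift in one arm's baseline caused by knowing the arm, in SD units
- r: the correlation between baseline and post-T10 (equal SDs at both times)
- p: the share of the shift still present at post-T10
- no true treatment effect

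The arms then differ by s at baseline and by p·s at post-T10.

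- Change-score contrast: p·s − s = −s(1 − p)
- Baseline-adjusted contrast: p·s − r·s = s(p − r)

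The two extremes are:

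- Shift vanished (p = 0): change −s, adjusted −r·s
- Shift fully persisting (p = 1): change 0, adjusted +s(1 − r)

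| s | change, p = 0 | change, p = 1 | adjusted, p = 0 (r = 0.3 / 0.5 / 0.7) | adjusted, p = 1 (r = 0.3 / 0.5 / 0.7) |
|---|---|---|---|---|
| 0.1 | −0.10 | 0 | −0.03 / −0.05 / −0.07 | +0.07 / +0.05 / +0.03 |
| 0.2 | −0.20 | 0 | −0.06 / −0.10 / −0.14 | +0.14 / +0.10 / +0.06 |
| 0.3 | −0.30 | 0 | −0.09 / −0.15 / −0.21 | +0.21 / +0.15 / +0.09 |

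The sign of the adjusted bias changes at p = r.

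**Scale for comparison.** The article classes d = 0.20 as small. With 21 dyads per arm, the standard error of an unadjusted standardised difference is √(2/21) = 0.31. After baseline adjustment it is 0.31 × √(1 − r²), that is 0.27 at r = 0.5 and 0.22 at r = 0.7. For s = 0.2, the adjusted bias at these two values of r (0.06 to 0.14) is therefore below the sampling error. Unlike sampling error, it would not shrink in a larger trial run in the same order.

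**The case against.** The case for leaving the plan alone has several sound parts.

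- **Not every baseline value is at risk.** Age and sex cannot change because an envelope was opened, and the diagnosis is recorded at screening.
- **Not every change estimate is at risk.** A reader might infer that all within-subject results are affected. Contrast B starts from post-intervention and does not use the baseline.
- **The proposed primary outcome is partly protected.** Blinded raters score a manualised task, so arm knowledge can reach the APCI only through how the dyad behaves.
- **The self-reports are not equally exposed.** BAS looks back 6 months, EXIS 2 weeks and KINDL one week. These windows may cover time before disclosure, and dyads are not told the hypotheses.
- **Early disclosure may have a use.** Right after allocation, the Screening section has the team choose an outpatient or inpatient setting. The therapist pool also supplies the APCI assessors, and a dyad's assessor must not be its therapist. It would be wrong to say that early disclosure serves no purpose.
- **Early drop-out is not overlooked.** It is counted before pre-T1 and reported by arm and cause.
- **Re-ordering does not remove arm awareness at post-T10.** It removes the baseline's part (−s or −r·s); any persisting part p·s remains.
- **The trial is exploratory.** Its main questions concern recruitment, retention, adherence and blinding, and the article defers reliable effectiveness statements to the main trial.

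These arguments limit the reach and severity of the point. They do not change the order of events. The free-text goals have neither a blinded rater nor a stated look-back window to protect them, and the staffing argument bears on T1/T2 far more than on a paper survey.

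**Conclusion.** The concern holds in limited form. As written, GAS, KINDL, EXIS, BAS, SCL-9k, WIRF and the baseline APCI are all measured after disclosure, yet they serve as the start of Contrast A and as covariates. The risk is greatest for GAS goals, lower for the other self-reports, and for the APCI confined to dyad behaviour.

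A reader might infer a known bias of about 0.2 SD, as large as the article's own small effect. The documents do not support that. The 0.2 SD is an assumption, and it carries full weight in a change score only if the shift has gone by post-T10. If it persists completely, the change-score bias is zero and the adjusted bias reverses sign. Both size and direction are therefore unknown.

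The point should be fixed, because the remedy is cheap and the effect estimates feed a later sample size calculation. It does not invalidate an exploratory feasibility trial. The reading of the sequence rests on the text and Table 2, without sight of Fig. 1.

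**What to change.** In Screening and Treatment allocation, state that the envelope is opened only after the pre-T1 survey, including the GAS goals, has been completed by child and significant other and filed. Opening it after T2 would also protect the baseline APCI. This is optional, to be done if the setting decision and therapist staffing allow.

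Recruitment was under way at publication, so for dyads already enrolled under the present order:

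- keep them in the main intention-to-treat analysis;
- flag their outcome baselines as post-disclosure;
- add a sensitivity analysis either without these dyads or without adjustment for outcome baselines.

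**Cost.** Existing steps are re-ordered by a short amendment, and families and therapists learn the arm slightly later. The trial would contain two baseline regimes, which must be reported. Leaving out the early dyads could remove much of a sample of 52. Dropping the baseline adjustment loses precision: the standard error is 0.31 instead of 0.22 to 0.27 for r = 0.7 to 0.5.

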#### Baseline (pre-T1, T1/T2)

The paper–pencil baseline survey will be completed by all children (approx. 10 to 15 min) and significant others (approx. 20 to 30 min) (pre-T1), i.e. up to a maximum of 3 days prior to the APCI with its two manualized entry music therapy sessions (approx. 25 min each) (T1/T2). The APCI music therapy sessions will be video-recorded and evaluated using the APCI online programme. APCI raters are blinded and will give information about possible significant moments in T1/T2 and about their adherence to the APCI manual based on self-evaluation. The child and significant other will also provide information about their significant moments if present. Two independent student raters will rate one of the two APCI sessions for APCI manual adherence.

#### Therapy (T3 bis T9)

The music therapy interventions will be provided in seven sessions (T3 to T9). They will last about 20 to 45 min, will be video-recorded, and descriptively documented by the music therapists. At the end of each music therapy session, the child, significant other, and music therapist will give information about significant moments. The music therapists will self-evaluate their adherence to the INMUT-KB or MUT-K manual. Two independent student raters will rate two of the seven intervention sessions for INMUT-KB or MUT-K manual adherence.

#### Outcome (T10, post-T10)

The final APCI session (T10) will last about 25 min, will be video-recorded, and evaluated using the APCI online programme. APCI raters are blinded and will give information about significant moments in T10 and a self-evaluation on their adherence to the APCI manual. The child and significant other will provide information about their significant moments. Two independent student raters will rate the final APCI session for APCI manual adherence.

The paper–pencil outcome survey will be completed by all children (approx. 10 to 15 min) and significant others (approx. 20 to 30 min) (post-T10), i.e. up to a maximum of 24 h after the final APCI.

#### Follow-up (cat-T11)

A paper–pencil follow-up survey will be completed 3 months after the last APCI was carried out by all children (approx. 10 to 15 min) and significant others (approx. 20 to 30 min) (cat-T11).

### Randomization

#### Treatment allocation

We will use block randomization of 10 to 12 child-significant other dyads each. From the total of 52 child-significant other dyads to be included, 21 dyads will be randomly assigned to the INMUT-KB, 21 dyads to MUT-K, and 10 dyads to WLG. The randomization plan will be carried out by an independent research assistant at the Heidelberg University Hospital, who is not otherwise involved in the study, using the statistical software R version 4.2.1 [36, 37]. The randomized allocation of the child-significant other dyads into the three study arms will be performed after finalization of the screening. The allocation will be carried out by means of sealed envelopes (“sealed envelope method”), which will be opened in the presence of the child-significant other dyads together with a study staff member.

### Blinding and Allegiance

#### Blinding

The APCI sessions at baseline (T1/T2) and end of therapy (T10), indicating the primary endpoint of this feasibility RCTs, will be blindly conducted by APCI raters. The music therapists will know the assignment as they will also guide the INMUT-KB and MUT-K (T3 to T9). APCI raters will not be the music therapists who are otherwise working with the child-significant other dyads. The included child-significant other dyads will be informed about their assignment and the general aims of the study, but not about specific hypotheses of any endpoint.

#### Allegiance

Researchers’ and therapists’ preference for a particular treatment can lead to bias in the outcome data [38]. To avoid such bias, we will use multiple music therapists in the role of APCI assessors and/or INMUT-KB and MUT-K music therapists. They come from different music therapy traditions and are open to use their method but must be loyal to the INMUT-KB and MUT-K music therapy manual, respectively. They will all receive equal support and contribute equal numbers of hours and child-significant other dyads to the project [39].

### Music therapy intervention

#### Manual

The process-oriented music therapy interventions are methodologically oriented towards Nordoff/Robbins, Neugebauer, and Aldridge [40–42] but take into account the different practical experiences of the respective therapists. The process orientation serves the stimulation of creativity in music therapy and offers space for (1) the use of melodic, harmonic, and rhythmic instruments that can be played and freely chosen without prior knowledge; (2) individual session lengths adapted to the needs of the child and significant other, if present; (3) objectives tailored to the participant(s); (4) taking up topics of the participant(s) and integrating them into the interventions; (5) situational decisions about both active and receptive offers; (6) promoting relationship work in musical improvisation; and (7) linking to individual resources of the child and significant other, if present. The focus is the relationship work in musical improvisation. While this develops between child and music therapist in the individual sessions (MUT-K), during the multi-person setting, the focus is on the musical togetherness in the child-significant other dyad (INMUT-KB). The goal is that the same significant other attends all music therapy interventions. In exceptional cases, a change of significant others is permitted. For a better reflection, all music therapy sessions will be video-recorded. The therapists offer to watch the recordings together with the families to formulate significant moments. The overall process of the music therapy intervention is presented to the interprofessional team of our cooperating clinics and the research team in a descriptive report written by the music therapists.

#### Adherence

The therapists will self-evaluate their adherence to the music therapy manuals (INMUT-KB, MUT-K) after each session. In addition, two independent student raters will rate selected sessions for manual adherence.

### Measures

As the purpose of this study is to explore the feasibility of a fully powered RCT, we will use different measures, including both qualitative information and quantitative data.Feasibility and acceptability of research methodology*RQ1.1*: The feasibility analysis of the protocol implementation focusses on the overall recruitment target of the child-significant other dyads (*n* = 52), as well as the specific recruitment target for each study-arm INMUT-KB (*n* = 21), MUT-K (*n* = 21), and WLG (*n* = 10). The study considers the estimation of the total sample to be recruited, the overall dropout rate, and the differentiated dropout rate within the study arms at all measurement times. Data will be collected by observing the participant flow: Counting the number of study participants who (1) are recommended for inclusion by the medical team; (2) are contacted by the study staff to provide information about the feasibility RCT; (3) give their consent to study participation; (4) will be included into the study; (5) drop out before the baseline survey (pre-T1); (6) complete the baseline survey (pre-T1); (7) drop out before or during the baseline APCI ratings (T1/T2); (8) complete the baseline APCI ratings (T1/T2); (9) drop out before or during the INMUT-KB, MUT-K, and WLG (T3–T9); (10) complete INMUT-KB, MUT-K, and WLG (T3–T9); (11) drop out before the final APCI rating (T10); (12) complete the final APCI rating (T10); (13) drop out before the outcome survey (post-T10); (14) complete the outcome survey (post-T10); (15) drop out before the 3-month follow-up survey (cat-T11); and (16) complete the 3-month follow-up survey (cat-T11). We will describe the causes for dropout and calculate the retention rate for the three study arms separately and together. Success is defined as attaining 100% and retaining 75% of the planned sample.*RQ1.2*: The feasibility of this RCT depends on the recruitment of a sufficient number of music therapists. We expect around five to six cases per music therapist, so that successful recruitment will involve at least seven to eight music therapists. For professional support, every third session will be supervised; based on the case numbers, we are planning 108 supervised sessions.*RQ1.3*: Certification to use the APCI was started by seven music therapists and successfully completed by five. The APCI raters were trained in the practical application of the APCI manual, video analysis, data collection, and statistical analysis. Experience-based receptive interviews [43] with APCI raters will gather information about the circumstances that contribute to successful APCI implementation. The success of APCI blinding will also be evaluated in receptive interviews. For professional support, every third APCI session will be supervised; based on the case numbers, we are planning 49 supervised sessions.

2.Feasibility and acceptability of the interventions*RQ2.1*: The feasibility and acceptance of the APCI ratings (T1, T2, and T10) by study families are assessed by analysing the therapists’ final APCI descriptions.*RQ2.2*: How well APCI raters implement the APCI ratings (T1, T2, and T10) is assessed by their self-assessment after each APCI session using an APCI manual adherence scale (range: 0 to 100). In addition, randomly selected first or second sessions (T1, T2) and final sessions (T10) are evaluated by two independent observers.*RQ2.3*: The feasibility and acceptance of the music therapy interventions (T3–T9) by study families are assessed on a visual analogue scale (range: 0 to 100), complemented by experience-based reports in receptive interviews [43] conducted with the study families during the study period. In particular, the needs of the child-significant other dyads are analysed with a special focus on the involvement of significant others in the music therapy process. Compliance with the INMUT-KB and MUT-K conditions by the children and significant others is assessed based on the percentage of attempted and completed music therapy sessions. Compliance with the WLG is assessed according to whether alternative music therapy interventions outside the trial were used during the waiting period.*RQ2.4*: How well music therapists implement the music therapy interventions (T3–T9) is assessed by their self-assessment after each session using an intervention manual adherence scale (range: 0 to 100). In addition, every third session is evaluated by two independent observers.*RQ2.5*: Additional identified benefits and barriers of INMUT-KB, MUT-K, and WLG will be monitored throughout the study and considered in relation to intervention safety and potential adverse outcomes, in addition to experience-based reports in receptive interviews [43]. For any undesirable psychological and/or somatic effects during or after the music therapy interventions, psychological psychotherapists at the Centre for Mental Health and Psychotherapy (ZPP) at the UW/H, directed by [name]. [name], will be available.

3.Estimation of effect sizes*RQ3.1*: The potential effect of including significant others is measured using the quantitative and qualitative data of the APCI ratings, including its three subscales and the final score, at baseline (T1 and T2) and final assessment (T10)*.**RQ3.2*: The estimation of effect size and 95% CI for change will concentrate on the proposed primary outcome, i.e. APCI subscores of mutual attunement, nonverbal communication, and parental emotional response from baseline to the end of music therapy.*RQ3.3*: The estimation of effect size and 95% CI for change will concentrate on the proposed secondary outcome, i.e. subjective goal achievement, quality of life, system-related functional level, psychosocial stress, psychosomatic complaints, and resources from baseline to the end of music therapy.

